### Randomisation and blinding

Stratification will be applied by etiology (CNS- or CNS+), age in years (7–9; 10–12; 13–16), center (Zurich or Bern) and nonverbal IQ (IQ < 93.5; IQ 93.5–106.5; IQ > 106.5) using the minimization randomization method [82] comprised in SecuTrial®. The allocation, enrolment and assignment will be carried out by RE. Participants with physical restraints (e.g. remaining paresis after surgery) who are unable to perform physical activities will be assigned to group A or C. Because this assignment breaks the randomization, these participants will be excluded from between-groups comparisons and will be analyzed only exploratively. Investigators assessing participants at T2 and T3 will be blinded with regard to treatment assignment of the participants. If there is any premature unblinding (e.g., accidental or due to a serious adverse event) the investigator has to promptly document and explain to the sponsor.

### Data analysis

The data collected will be tested as to their statistical properties and analyzed accordingly. The level of significance is set to *α* = 0.05. Normally distributed background and control variables will be compared between the groups (experimental vs. control group) using two-sample *t*-tests, and variables without normal distribution will be tested using Wilcoxon rank-sum test. Chi-squared test will be used for categorical variables. The diary entries and the execution data obtained from the XBOX/ Cogmed RM® during training sessions will be used to provide information about the focus and the frequency of the training. These scores will be presented as descriptive summaries. The frequency and duration of exercises during the intervention period will then be compared between the experimental groups.

#### Behavioral data

Raw scores of cognitive tests will be transformed to standard scores, *T*-scores or Intelligence quotient (IQ)-scores using age norms from the respective test manuals. Subsequently, to make results comparable among different tests, *z*-scores will be computed. In order to compare the baseline performance between patients and controls, Analyses of Variance (ANOVAs) will be calculated. To examine training effects, primary and secondary outcome variables of T1, T2 and T3 will be analyzed using Analysis of Covariance (ANCOVA) comparing the three groups, in order to increase statistical power and reduce possible bias [83]. To test whether inter-individual differences predict training or transfer effects, linear regression analyses will be performed (predictor variables i.e. gender, age, kind of cancer, cancer treatment methods, IQ).

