### Study aims and hypotheses

The purpose of this study is twofold: First, the availability of well-designed, child-friendly, and evidence-based training is of major clinical relevance and will contribute to the prevention of a further decline of cognitive functions and scholastic problems. Therefore, this study will compare the efficacy of two different trainings aiming to foster cognitive performance in pediatric cancer survivors. As primary outcome, we hypothesize that both trainings (computerized working memory training and exergaming) lead to improvements in core EF performance (inhibition, shifting and working memory) compared to a control condition. As secondary outcome, near and far transfer effects of both trainings are expected immediately after the training and at 3-months follow-up.

Second, the detection of training-induced changes in brain structure and function will give insight into the training related plasticity of the child’s brain. As further secondary outcome, the relationship between training related cognitive change and training related change in brain structure and function will be examined.

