## Methods

### Design

The study is designed as a randomized stratified controlled trial including three experimental groups (computerized working memory training, exergaming, waiting control group) consisting of pediatric cancer survivors and a healthy control group without intervention (matched for age, gender and socioeconomic status). For cross-sectional evaluation of cognitive performance, cancer survivors and healthy participants will be compared in a baseline assessment. For longitudinal evaluation, only cancer survivors will be randomly assigned to either intervention group A (computerized working memory training), intervention group B (exergaming) or the waiting control group C (see Fig. 1). Cognitive and physical assessment will be carried out before the interventions and the waiting period (baseline assessment; T1) and will be re-performed with all participants after 8-weeks at immediate follow-up (T2) and at a 3-month follow-up (T3). Structural and functional imaging will be performed at each time-point (T1-T3).

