### Interventions

All 150 participants with a history of cancer will be randomly assigned to one of three experimental conditions (A, B, and C). The participants in the experimental conditions (A, B) will absolve three training sessions per week for a period of 8 weeks of their respective training; each session takes about 45 min. The difficulty level of the trainings (A, B) is adaptive and adjusted based on the user’s performance. Each participant will thus absolve a total of 25 training sessions (including the supervised first training session) of individually adapted difficulty levels. The training will be supervised by training aides (parent or guardian) and trained coaches. In both trainings, a coach will provide weekly supervision via phone call to the child’s home.

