***Group C***
*(n*_*1*_ *= 25 CNS+, n*_*2*_ *= 25 CNS-)* will serve as a waiting control group and will receive either the physical or the computerized working memory training program after completion of the immediate follow-up assessment.

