Immediate follow-up (T2): Pediatric cancer survivors will be re-assessed with the same tests and MRI protocols as in T1, shortly after termination of the 8-week intervention phase. If available, parallel test versions will be used for the assessment at this time-point and at follow-up. In addition to evaluate the overall acceptability and feasibility of the conditions, parents and participants will be given satisfaction questionnaires based on the questionnaires developed by Cox et al. [19].

3-month follow-up (T3): The three experimental groups will be re-assessed again at a 3-months follow-up with the same tests and same MRI protocol as in T1 and T2, to investigate the time dependent effect of the different training regimens.

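### Group C is trained after T2, so the planned three-group comparison at T3 sets earlier against later training, not training against no training

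*Protocol article*

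**What the plan says.** All statements are in the protocol article.

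- **Group C (Interventions).** The waiting control group "will receive either the physical or the computerized working memory training program after completion of the immediate follow-up assessment". The immediate follow-up assessment is T2, 8 weeks after baseline.
- **Interventions.** A course in groups A and B consists of "three training sessions per week for a period of 8 weeks of their respective training".
- **3-month follow-up (T3), in the text after Functional imaging.** "The three experimental groups will be re-assessed again at a 3-months follow-up with the same tests", and the stated purpose is "to investigate the time dependent effect of the different training regimens".
- **Behavioral data.** The rule for testing training effects reads: "primary and secondary outcome variables of T1, T2 and T3 will be analyzed using Analysis of Covariance (ANCOVA) comparing the three groups". Group C has no different role at T3.
- **Study aims and hypotheses.** The primary hypothesis is that both trainings "lead to improvements in core EF performance (inhibition, shifting and working memory) compared to a control condition". The 3-month time point is named in a separate sentence on the secondary outcome, which reads: "near and far transfer effects of both trainings are expected immediately after the training and at 3-months follow-up".

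**The concern.** A waiting-list control serves as an untrained comparator only while it waits. Here the wait ends after T2, but the analysis sentence carries the same three-group comparison on to T3 under the same purpose of examining training effects. No other untrained group exists at T3: under Outcome measures and time-points of assessments, the healthy controls take part only in the activity monitoring before baseline and in T1.

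What is at stake is how the 3-month result is read. Suppose both trainings work, the benefit lasts, and group C then improves through its own training. The groups converge at T3, and a reader who takes the T3 contrast as training against control would conclude that the benefit has faded. Group C also receives either programme, so each T3 contrast with C is partly a programme set against itself at a later date.

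**Working it through.** **1. Timing.** Inputs are an 8-week course (Interventions), a start for group C after T2 (Group C) and a 3-month follow-up at T3 (Design).

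- Course length: 8 × 7 = 56 days. Three months: about 91 days.
- If the 3 months run from T2, 91 − 56 = 35 days are left over, so a course begun promptly after T2 is finished before T3.
- If they ran from baseline, T3 would fall about 91 − 56 = 35 days after T2, and C would be part-way through its course.
- If T3 for group C were counted from its own training, C would be trained by definition.

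C would be untrained at T3 only if its training were withheld until after T3. The article does not say so.

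**2. The plan's own figure.** The section on cancer survivors gives minimum sizes of 14 (inhibition, shifting; retest reliability 0.77) and 22 (working memory; 0.62) per group, for six groups, two time points, 80% power and α = 0.05. For the group-by-time interaction of a repeated measures ANOVA, the noncentrality is f²·N·m/(1 − ρ) with m = 2, on (k − 1)(m − 1) and (N − k)(m − 1) degrees of freedom with k = 6. Taking f = 0.14 (an assumption, since the article gives no number for a small effect), this returns exactly 14 and 22. With f = 0.10 it returns 26 and 42. The point does not depend on this figure. What matters is that the sizing uses two time points, before and after training or waiting, which matches T1 and T2, when C is untrained.

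**3. Expected contrast at T3.** Let d be the true training effect, kept in full by A and B to T3, and let C gain a share c of d from its own training. Then

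E(A − C at T3) = d − c·d = d(1 − c).

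**4. Power when T2 has 80%.** Two-sided α = 0.05 is assumed, because the article does not state sidedness. By normal approximation, 80% power means d/SE = 1.960 + 0.842 = 2.802. With the same SE at T3 and c = 0.5, the ratio is 1.401 and power is Φ(1.401 − 1.960) = Φ(−0.559) = 0.29. This result does not depend on the sample size or the reliability. With c = 1 the expected contrast is 0.

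**5. Power at the planned arm size.** There are 25 + 25 = 50 per arm. SE = √(2(1 − ρ²)/50):

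- ρ = 0.77: √(2 × 0.4071/50) = 0.128
- ρ = 0.62: √(2 × 0.6156/50) = 0.157

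With an assumed d = 0.5 and power = Φ(d(1 − c)/SE − 1.960):

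| Share c gained by C | Expected T3 contrast | Power, ρ = 0.77 | Power, ρ = 0.62 |
|---|---|---|---|
| 0 | 0.500 | 0.98 | 0.89 |
| 0.25 | 0.375 | 0.84 | 0.67 |
| 0.5 | 0.250 | 0.50 | 0.36 |
| 0.75 | 0.125 | 0.16 | 0.12 |

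If A and B had also lost part of their gain by T3 while C was freshly trained, the contrast could be smaller still, or negative.

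**The case against.** **The primary comparison is protected.** The sample size rests on two time points before and after training or waiting. The 3-month effect is named only under the secondary outcome, in a sentence that does not repeat the comparison with a control condition. The stated purpose of T3, a time-dependent effect, can be met by comparing A with B and by looking at retention. This largely stands: a T1-adjusted comparison at T2 is against an untrained group and is sound. It does not remove the T3 problem, because the analysis sentence names T3 for primary and secondary variables alike.

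**A reader might infer that the primary result itself is biased towards zero.** The documents do not support that. Dilution would occur only if one group effect were pooled over T2 and T3; with C fully trained at T3, an equal-weight average would be (d + 0)/2 = d/2. Separate ANCOVAs at T2 and T3, or a joint model with group-by-time terms, fit the sentence equally well and leave the T2 contrast intact. Pooling is neither stated nor ruled out.

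**A reader might also infer that a T3 difference from C means nothing.** That goes too far. The arms are randomised, so the difference estimates early against delayed training. The fault lies in reading it as training against no training.

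**The timing is inferred, and detail may sit elsewhere.** The article does not say that C starts at once or finishes before T3, and Fig. 1 is not shown. How each child's programme in group C is chosen can properly be left to the full protocol and carries no weight here. The point rests on the stated three-group comparison at T3, not on missing detail.

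**Conclusion.** The concern holds for T3. As written, the plan examines training effects at T3 by comparing three groups, one of which has by then most likely received one of the two trainings. The contrasts with C at T3 therefore estimate earlier against later training, and a lasting benefit could be reported as fading.

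The size depends on how much C gains, which the article cannot tell us. At half the effect, 80% power at T2 becomes about 29% at T3; at the full effect, nothing is left to detect although both trainings work. These figures are illustrations. They assume that A and B keep their full effect, that the standard error is the same at T2 and T3, that tests are two-sided, and that C starts its course soon after T2. The T2 comparison is not impugned.

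**What to change.** Amend the wording under Behavioral data and under Study aims and hypotheses:

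1. State that the controlled contrasts A − C and B − C are estimated at T2 by ANCOVA adjusted for the T1 score, and are not pooled with T3.
2. At T3, report A versus B, adjusted for T1. Both arms were randomised and trained over the same period.
3. Report T2-to-T3 retention within A and within B, described as uncontrolled change.
4. If a T3 contrast with C is shown, label it early versus delayed training.
5. Reword the 3-month hypothesis so that it speaks of retention and of A against B, not of an effect relative to an untrained group.

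This adds no participants or visits and leaves the interventions as they are. The cost is giving up a controlled 3-month claim, which the design does not support because group C is trained after T2. The wording should be settled before the T3 data are analysed.

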#### Neuroimaging data

Pre- and post-processing of structural and functional data will be performed using SPM12 (Welcome Departement of Imaging Neuroscience, London) and MATLAB programs (MATLAB version 8.3). In order to perform functional connectivity analyses, the GIFT Toolbox will be used and within the framework of Independent Component Analysis (ICA) using the Group ICA Toolbox (GIFT software) [84] in order to compute the feature of the resting state network and the functional connectivity network. Functional magnetic resonance imaging of working memory will be analysed using SPM. After slice timing, spatially realignment and unwarping, data will be normalized using custom-generated pediatric reference data (TOM-toolbox; [85]). Images will be smoothed by a Full Width at Half Maximum Gaussian kernel. First level analyses will be conducted using the General Linear Model contrasting the active and baseline conditions. Resulting contrast images will be entered into a random-effect second level analysis, applying one-sample *t*-tests. The fractional anisotropy maps resulting from the diffusion sequence are provided by the Siemens software and can be used for further statistical evaluation of relative longitudinal comparisons on a single- subject level. ASL will be analyzed on a single-subject level; afterwards the resulting relative cerebral blood flow (rCBF) values will be used for further statistical group analyses.

#### Missing data

Missing data will be imputed for the respective analyses. Data missing completely at random will be replaced by Expectation-Maximization (EM) algorithm. If data is not missing completely at random, a multiple imputation will be applied.

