### Participants

#### Cancer survivors

In total, 150 children and adolescents aged 7–16 years with a previous diagnosis of cancer with or without CNS involvement (CNS+ and CNS-) in the past ten years and terminated their treatment (surgery, radiation, and/or chemotherapy) at least 12 months prior to participation will be included in the study. Cancer survivors will be recruited at two specialized pediatric university hospitals in Zurich and in Bern, Switzerland. To reduce the heterogeneity of the sample, participants with a history of cancer without CNS involvement and only surgical removal of the tumor without subsequent radiation and/or chemotherapy will be excluded from the study. The sample size was calculated for the primary outcome measures of inhibition, shifting (Color-Word Interference Test; retest-reliability = .77) and working memory performance (Block Recall Test; retest-reliability = .62), both will be assessed before and after the trainings and before and after the waiting period. Sample size calculation was performed using G*Power 3 [58], based on a repeated measures ANOVA with small effect sizes (six groups; two time points; statistical power = 80%; *α* = 0.05), resulting in a minimal sample size of 14 (for inhibition, shifting) and 22 (for working memory) in each group. In order to compensate for losses/drop outs, sample size was defined at 25 patients per group.

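### Single EM replacement of data judged missing completely at random gives the group comparison either standard errors that are too small or a shrunken training effect, depending on whether arm is in the EM model

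*Protocol article*

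**What the plan says.** The Missing data section states that missing values will be imputed and gives two rules. For the first kind: "Data missing completely at random will be replaced by Expectation-Maximization (EM) algorithm". For the rest: "If data is not missing completely at random, a multiple imputation will be applied". It does not list the variables in the EM model. It also does not say that the uncertainty of the replaced values is carried into later tests.

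The completed data feed the analysis under Behavioral data, an ANCOVA of the primary and secondary outcomes across the three arms. Under Data analysis, "The level of significance is set to *α* = 0.05".

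No drop-out rate is given. The section on cancer survivors reports a calculation "based on a repeated measures ANOVA with small effect sizes" ("six groups; two time points; statistical power = 80"%), "resulting in a minimal sample size of 14 (for inhibition, shifting) and 22 (for working memory) in each group". It then sets 25 per group to cover losses. The groups are the six arm-by-etiology cells, so each arm has 50 children.

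**The concern.** An EM-replaced score is a predicted value that the ANCOVA counts as an observed child. With arm among the predictors, the filled-in children lie on the fitted line. They add nothing to the residual sum of squares but are counted in the sample size, so the standard error is too small. Without arm among the predictors, the filled-in children of every arm are placed on a common line, and the difference between arms is pulled towards zero.

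The rule applies when data are missing completely at random, and in that case an ANCOVA of the observed scores is already valid. The replacement therefore adds error where none existed. What is at stake is either the false-positive rate or the size of the reported training effect on the primary executive function outcomes.

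**Working it through.** **Inputs from the article**
- Two-sided α = 0.05 (sidedness is not stated; two-sided assumed).
- Three arms of 50.
- Retest correlations: "Color-Word Interference Test; retest-reliability = .77" and "Block Recall Test; retest-reliability = .62".
- Minimal cell sizes 14 and 22, raised to 25.

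**The plan's own figures.** The article calls the effect small but gives no number. A noncentral-F calculation for the group-by-time interaction (six groups, two time points, power 80%) returns exactly 14 and 22 per group at f = 0.14. The conventional small f = 0.10 returns 26 and 42. The loss margins follow directly:
- working memory: 1 − 22/25 = 12%
- inhibition and shifting: 1 − 14/25 = 44%

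Neither is a stated drop-out rate. I take 12% as the working assumption and show 20% beside it.

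**Case 1: arm in the EM model.** Let d be the missing fraction, n the arm size and σ² the residual variance given T1. Only the n(1 − d) observed children contribute residuals, but the ANCOVA divides by about n:
- reported SE ≈ √(2(1 − d)σ²/n)
- true SE ≈ √(2σ²/(n(1 − d)))
- ratio ≈ 1 − d

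With r = .62, σ² = 1 − 0.62² = 0.6156. At n = 50 and d = 0.12:
- reported SE = √(2 × 0.88 × 0.6156/50) = 0.147
- true SE = √(2 × 0.6156/44) = 0.167

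Type I error for a pairwise contrast is 2(1 − Φ(1.96(1 − d))). For the three-group test it is P(χ²₂ > 5.991(1 − d)²).

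| Loss d | Pairwise | Three-group |
|---|---|---|
| 5% | 6.3% | 6.7% |
| 12% | 8.5% | 9.8% |
| 20% | 11.7% | 14.7% |

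This was checked by simulation: T2 regressed on T1 and arm, arms of 50 and 25, r = .62 and .77, 4,000 runs per setting, no true effect, with EM including arm or run separately by arm. At 12% loss, type I error was 7.5-9.6% pairwise and 9.2-10.5% for the three-group test. A separate simulation with 3,000 runs gave 7.7-8.5% and 9.1-10.3%, with standard errors about 11% too small.

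**Case 2: arm left out of the EM model.** The missing fraction of each arm is filled from a common line, so the expected estimate is (1 − d) times the true effect: 0.88 × 0.40 = 0.352 SD. The simulated estimate was 0.351 SD, with a reported SE of 0.148 against an empirical SE of 0.149. Type I error was 4.3-5.0%.

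**Comparators.** An ANCOVA of observed cases held type I error at 4.4-5.4% and recovered 0.399 SD of a true 0.40 SD. Multiple imputation with arm in the model gave 4.4-5.3% (2,000 runs).

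**The case against.** Five points can be made on the other side.

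1. **The inflation is conditional.** It needs arm in the EM model, which the article does not state and may leave to the analysis plan. This stands. A reader might infer that the plan's false-positive rate is about 9%, but the text does not support that. Leaving arm out does not rescue the rule, because the estimate is then attenuated. In fairness, power is hardly affected in that case: at a true 0.40 SD and 12% loss the three-group test rejected in 67.6% of runs, against 67.1% for observed cases. The harm is to the estimate and its interval.

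2. **No drop-out rate is stated.** This stands, and 12% is an assumption. The 44% margin, at which the same formulas give 27% and 39%, is equally tempting. It is only the surplus that inhibition and shifting gain because all cells are set at 25, and it is not an expected loss.

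3. **The loss pattern may be milder.** The calculation gives missing children no later score to help the prediction. If T3 is observed, type I error with arm in the model is smaller: 7.3% at 12% loss with r = .77, and about 5.5-6% at 5% loss. This stands as a limit on size.

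4. **Replacement might include a random residual.** The article's wording suggests otherwise. Even so, adding one draw still gave 7.9-8.3% at 12% loss, because it remains single imputation.

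5. **The EM branch may seldom be used.** A reader might infer that EM becomes the default, since a non-significant test in 150 children cannot establish that data are missing completely at random. The article names no such test and no rule that a non-significant result selects EM, so that is supposition. It also assigns multiple imputation to all other missing data, which confines the defect to one branch.

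**Conclusion.** The point holds. It concerns a rule that the article states, not a detail left out. Under the natural reading (one completed data set, analysed as observed), the EM branch damages the group comparison under either specification of the EM model:
- **Arm included:** standard errors are about 11-12% too small at 12% loss. Type I error is about 8-9% pairwise and 9-10% for the three-group test, rising to about 11-12% and 15% at 20% loss.
- **Arm excluded:** type I error is near 5%, but the effect shrinks by about the missing fraction (0.40 SD to about 0.35 SD at 12% loss).

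These sizes assume the stated loss rates, loss unrelated to the outcome, approximately normal scores and an ANCOVA of T2 on T1 and arm. Which of the two harms would occur cannot be settled from the article. The change should be made, but the defect is limited to one branch and its size depends on a loss rate that is not stated, so it does not by itself undermine the trial.

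**What to change.** Delete the EM branch and use one method for all missing outcome data, without any judgement of whether they are missing completely at random. Either of these would do:
- **Multiple imputation**, which the plan already foresees. The imputation model should contain arm, the T1, T2 and T3 scores and the minimisation factors (etiology, age band, center, nonverbal IQ band), with results combined by Rubin's rules. Arm should be allowed a separate effect at T2 and T3, because the waiting group is trained after T2.
- **A likelihood-based mixed model** on all observed scores, with arm by time and the same factors.

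Possible wording: *Missing outcome data will be handled by multiple imputation whatever the assumed mechanism; the imputation model will include treatment arm, all assessments of the outcome and the minimisation factors, and estimates will be pooled by Rubin's rules.*

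The cost is one sentence, with no new data and no extra participants. Compared with EM replacement that includes arm, confidence intervals become wider by a factor of about 1/(1 − 0.12) = 1.14 at 12% loss. That is the width they should have had.
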